The primary efficacy endpoint will be the T1 overall VAS score. The primary analysis will use an analysis of covariance model. The T1 VAS score will be used as the dependent variable, group will be included as a fixed factor, and baseline VAS score will be included as a covariate. The adjusted mean difference in T1 VAS score between the two groups will be reported with the 95% confidence interval and *p* value. Descriptive results for the change from baseline to T1 will also be reported. At T1, the proportions of participants achieving a reduction of ≥1.4 cm from baseline in the overall VAS and an overall VAS score of ≤3.0 cm will be summarized by treatment group. Between-group differences will be evaluated using the chi-square test or Fisher’s exact test, as appropriate. Risk ratios and risk differences will be reported with 95% confidence intervals. These responder analyses will be considered supportive and exploratory.

To evaluate treatment trends over time, linear mixed-effects models will be used for continuous repeated-measure outcomes, including the overall VAS, component-specific VAS ratings, SPADI, CMS, and ROM. The models will include group, time, group-by-time interaction, and the corresponding baseline value. Participant will be included as a random effect. Time will be treated as a categorical variable. An unstructured covariance structure will be preferred. If the model does not converge, an appropriate covariance structure will be selected according to model fit indices. The group-by-time interaction will be used to evaluate whether treatment trends differ between the two groups across time points. The between-group difference in the primary outcome at T1 will be the main focus. Between-group differences in changes from baseline at T2 and T3 will also be reported for each outcome.

The component-specific VAS ratings for resting pain, activity-related pain, and nocturnal pain will be analyzed as exploratory secondary outcomes. Between-group differences at T1 will be estimated using analysis of covariance with adjustment for the corresponding baseline pain score. Changes over time will be explored using linear mixed-effects models including group, time, group-by-time interaction, and the corresponding baseline value. Effect estimates and 95% confidence intervals will be reported, and these analyses will be interpreted as exploratory.

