### Intervention standardization and outcome selection

3.3

This trial will keep all intervention factors as consistent as possible between the two groups, except for EA frequency. These factors include acupoints, needle specifications, insertion methods, de qi requirements, connected acupoints, waveform, needle retention time, treatment frequency, TDP irradiation, and treatment setting. This design will help isolate EA frequency as the key variable and reduce confounding from other treatment factors.

Both groups will receive the same TDP irradiation. Therefore, this trial will evaluate the relative efficacy of 2 Hz and 100 Hz EA under the same co-intervention setting. It will not evaluate the independent effect of TDP or the absolute efficacy of EA compared with no treatment, usual care, or sham acupuncture.

The VAS is selected as the primary outcome because pain is the most direct and core clinical manifestation of pain-dominant shoulder periarthritis, and it provides a simple validated measure of pain intensity (27). SPADI, CMS, and ROM will be used as secondary outcomes. These measures evaluate patient-reported pain and disability, overall shoulder function, and AROM and PROM, respectively (29–32). This outcome set can capture subjective pain experience, functional limitation, and recovery of shoulder mobility, thereby providing a more comprehensive evaluation than a single pain outcome.

This trial will use several follow-up time points. T1 corresponds to the end of treatment and will mainly assess early analgesic effects after the treatment course. T2 and T3 will be used to observe changes in pain, function, and ROM during short- and medium-term follow-up. Shoulder periarthritis has a staged clinical course, and pain relief, functional improvement, and ROM recovery may not occur at the same pace. Repeated assessments at multiple time points may help characterize the time course of treatment effects for different EA frequencies and provide evidence for evaluating the durability of treatment effects.

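### The repeated-measures model in 2.13 imposes one baseline slope on T1, T2 and T3; a baseline-by-time term would protect the precision of the exploratory contrasts almost for free (minor)

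*Protocol article*

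**What the plan says.** Section 2.13 of the protocol article gives the fixed effects of the linear mixed models for overall VAS, component VAS, SPADI, CMS and ROM: "The models will include group, time, group-by-time interaction, and the corresponding baseline value". It repeats the same list for the component ratings: "Changes over time will be explored using linear mixed-effects models including group, time, group-by-time interaction, and the corresponding baseline value". One interaction is named, group by time; baseline by time is not. On time and covariance it says "Time will be treated as a categorical variable" and "An unstructured covariance structure will be preferred".

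Two sentences say what the models are for: "The between-group difference in the primary outcome at T1 will be the main focus" and "Between-group differences in changes from baseline at T2 and T3 will also be reported for each outcome".

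The primary analysis is separate: an ANCOVA of the T1 overall VAS on group and baseline VAS, which estimates its own T1 slope. Section 2.13 calls secondary and follow-up analyses mainly exploratory. For SPADI, CMS and ROM it prefers either ANCOVA or mixed models.

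**The concern.** A baseline main effect without a baseline-by-time term assumes that a baseline difference of 1 unit predicts the same difference at 2, 8 and 24 weeks. A baseline score often predicts a near visit better than a distant one. If that holds here, the fitted slope is a compromise: it can be too steep for T3 and too shallow for T1. Part of the benefit of baseline adjustment is then lost, and at T3 all of it could be.

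Two things are at stake. One is the precision of the follow-up contrasts that the trial will report on durability. The other is agreement between the T1 VAS difference from the mixed model and that from the primary ANCOVA, because the two use different baseline slopes.

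**Working it through.** **The plan's own figure.** Inputs from 2.6: difference 1.0 cm, SD 2.0 cm, two-sided 0.05, power 0.80, 1:1, attrition 15%. By the noncentral t, power is 0.7952 at 63 per group and 0.8015 at 64. Then 64/0.85 = 75.3, so 76 per group and 152 in total. The stated figures reproduce. They concern T1 and take no credit for baseline adjustment, so this point does not touch them.

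**Inputs for the check.** From the protocol: the model terms, three post-baseline visits, SD 2.0 cm and 64 evaluable per arm. Not in the protocol, and therefore assumed: the correlation of baseline with each visit, the correlations between visits, and the SDs at other time points. Data are taken as complete.

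**Formulae.** Let s_0 and s_t be the SDs at baseline and visit t, ρ_t the correlation of baseline with visit t, b_t = ρ_t s_t/s_0 the true slope, and V the covariance of the three visits given baseline.

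- Common slope under an unstructured covariance: β_c = 1′V⁻¹b / 1′V⁻¹1, a weighted average of the three b_t.
- Variance per arm, up to 1/n: s_t²(1−ρ_t²) with visit-specific slopes; s_t²(1−ρ_t²) + s_0²(β_c−b_t)² with the common slope; s_t² unadjusted.
- With positive slopes, the common slope does worse than no adjustment only if β_c > 2b_t.

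**Equal SDs (set to 1), inter-visit correlations 0.6 (T1–T2), 0.6 (T2–T3), 0.45 (T1–T3).** The middle columns give the excess variance over visit-specific slopes.

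| ρ at T1/T2/T3 | Weights | β_c | T1 | T2 | T3 | T3 variance vs unadjusted |
|---|---|---|---|---|---|---|
| 0.60/0.45/0.30 | 0.515/0.238/0.247 | 0.490 | 1.9% | 0.2% | 4.0% | 0.95 |
| 0.70/0.50/0.30 | 0.594/0.238/0.168 | 0.585 | 2.6% | 1.0% | 8.9% | 0.99 |
| 0.85/0.60/0.30 | 0.763/0.276/−0.039 | 0.803 | 0.8% | 6.4% | 28% | 1.16 |

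Example, second row at T3: (0.585 − 0.30)² = 0.0812; 0.0812/(1 − 0.30²) = 0.0812/0.91 = 8.9%; and 0.91 + 0.0812 = 0.991 of the unadjusted variance. With equal slopes, β_c = b_t at every visit and the excess is zero.

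**Sensitivity to the inter-visit correlations.** With a T1–T3 correlation of 0.5, the second row gives β_c = 0.595 and (0.295)²/0.91 = 9.6%. The third row is unstable: β_c = 0.742 under 0.5/0.5/0.3 gives (0.442)²/0.91 = 21%, and β_c = 0.937 under 0.7/0.7/0.6 gives (0.637)²/0.91 = 45%. No single figure should be attached to steep decay.

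**Sensitivity to the SDs.** Take the first row with SDs of 1, 0.8 and 0.6 at T1, T2 and T3. The slopes become 0.60, 0.36 and 0.18, and β_c = 0.295. The T1 excess is (0.305)²/0.64 = 14.5%. The T3 excess is (0.115)²/(0.36 × 0.91) = 4.0%. The larger loss has moved to T1.

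**Simulation.** 8,000 trials per scenario, 64 per arm, SD 2.0 cm, no true effect. Mean contrasts lay between −0.008 and 0.008 cm, consistent with no bias. In the steepest scenario (0.60/0.30/0.10) the empirical SD of the T3 contrast was 0.370 cm with the common slope, against 0.354 cm with visit-specific slopes and 0.354 cm unadjusted. By the formula, T3 fell below no adjustment in that scenario and in 0.60/0.35/0.15, but not in 0.50/0.40/0.30 or 0.50/0.35/0.20.

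**Gap between the two T1 estimates.** It equals about (b_1 − β_c) × baseline imbalance. With a baseline SD of 2.0 cm, the imbalance has SD √(2 × 2.0²/64) = 0.354 cm and median absolute size 0.6745 × 0.354 = 0.238 cm. The first two table rows give 0.110 × 0.238 = 0.026 cm and 0.115 × 0.238 = 0.027 cm. In the simulated scenarios with decay, the median gap was 0.017 to 0.042 cm and the 95th percentile 0.072 to 0.137 cm, against a target difference of 1.0 cm.

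**The case against.** The strongest reply is that this is detail for the SAP, which section 2.14 says will be finalised before database lock, and that the affected contrasts are exploratory. The second half stands and limits the point to a minor one. The first half stands only in part: the protocol does not leave the fixed effects open but lists them twice, and that list gives a single slope.

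It is also fair that the loss is conditional. The document gives no correlations, and section 3.3 does not supply the missing evidence. Its remark that "pain relief, functional improvement, and ROM recovery may not occur at the same pace" compares different outcomes. It says nothing about whether baseline predicts one outcome less well as time passes.

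Three stronger readings may tempt a reader, and the text does not support them.

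- **T0 as a response level.** Because T0 is one of four assessment times and 2.13 does not say which times form the response, one might infer that T0 is both response and covariate, which would make the unstructured likelihood degenerate. Entering the baseline value as a covariate naturally implies post-baseline responses only. The inference rests on silence.
- **Every follow-up estimate depends on this model.** For SPADI, CMS and ROM, 2.13 also allows ANCOVA, and nonparametric tests or transformation if the data are clearly non-normal.
- **Two competing primary results at T1.** The ANCOVA is named as primary and the mixed model is there for trends over time. The small gap is a nuisance for reporting and creates no ambiguity about which result counts.

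**Conclusion.** The point holds as a minor matter of efficiency and consistency. Read as written, the model imposes one baseline slope on T1, T2 and T3. Randomisation keeps the contrasts unbiased, and the primary test, its significance level and the sample size of 152 are untouched.

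The possible loss depends on slopes that the document does not report. With equal SDs it falls mainly at T3: about 3–4% in variance under mild decay, about 9–10% and near break-even with no adjustment under moderate decay, and more only under steep decay, where the figure varies too widely to quote. T2 loses about 1% or less in the mild and moderate cases. If SDs shrink over time, the larger loss can move to the mixed model's T1 contrast, which is supportive only. If slopes are equal, nothing is lost. A reader should not conclude that the follow-up results will be imprecise or invalid, only that avoidable imprecision has been left in.

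**What to change.** In 2.13, and in the SAP, state that the responses are T1, T2 and T3 and that the fixed effects are group, time, group-by-time, baseline and baseline-by-time, for the component ratings as well. Add that the ANCOVA remains the sole inferential result for the T1 overall VAS and that the mixed-model T1 estimate is supportive.

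The cost is two extra parameters per outcome (three slopes instead of one), a few words of text and no new data.

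The change will not always make the two T1 estimates identical. They coincide only with complete data and an unstructured covariance. The plan allows for 15% attrition, and the mixed model also uses participants who lack T1 but have T2 or T3, which the ANCOVA cannot do without imputation. That is a further reason to name one of them as the inferential result.

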### Patient and public involvement, trial oversight, monitoring, and open science

2.14

No patient or public representatives were involved in the initial design of this trial protocol. Participant feedback collected during recruitment, treatment, and follow-up will be considered when refining future multicenter studies or optimizing the acceptability of the intervention procedures.

Changchun University of Chinese Medicine is listed as the applicant institution, and the Third Clinical Hospital Affiliated to Changchun University of Chinese Medicine will serve as the clinical study site and coordinating center for this single-center trial. Trial-related administrative matters will be coordinated by the study site and the principal investigator. The principal investigator, [name], will oversee the overall conduct of the trial. The coordinating center will be responsible for participant recruitment, intervention delivery, outcome assessment, safety management, data collection, and document storage. The data management team and independent statistician will be responsible for eCRF development, data checking, database locking, and statistical analysis. The funder will have no role in study design, trial conduct, data collection, data management, statistical analysis, interpretation of results, manuscript preparation, or the decision to submit the manuscript for publication.

A formal independent data monitoring committee will not be established because this is a single-center, low-risk, non-drug trial with a short treatment period. Safety and trial conduct will be reviewed by the principal investigator and the study team at regular quality-control meetings. No interim efficacy analysis is planned. The study may be temporarily suspended or terminated early in the event of unexpected safety concerns, serious protocol noncompliance, severe recruitment difficulty, or a decision by the ethics committee or study institution.

Important protocol amendments will be submitted to the ethics committee for approval before implementation and updated in the trial registry when applicable. Relevant amendments will be communicated to investigators, outcome assessors, data managers, and other trial personnel. If an amendment affects participant rights, safety, or study procedures, the informed consent form and other participant-facing materials will be revised accordingly.

The full trial protocol is reported in this manuscript. The detailed statistical analysis plan will be finalized before database locking and will be available from the corresponding authors on reasonable request. After publication of the trial results, de-identified participant-level data, the data dictionary, and relevant statistical code underlying the published findings may be made available from the corresponding authors on reasonable request, subject to ethics and institutional approval.

## Discussion

3

This study protocol describes a single-center, participant- and outcome assessor-blinded, parallel-group RCT. The trial will compare the efficacy and safety of 2 Hz and 100 Hz EA for pain-dominant shoulder periarthritis. Previous studies have mainly examined whether acupuncture or EA is effective for shoulder pain or frozen shoulder. This trial focuses on a more specific question: how EA frequency should be selected in this clinical stage. Under the same acupuncture prescription, treatment procedure, and co-intervention setting, the trial will compare the potential effects of two stimulation frequencies on pain relief, shoulder function, and range-of-motion recovery.

The trial will enroll patients with pain-dominant shoulder periarthritis and the Hand Shaoyang meridian pattern. This restriction is intended to improve clinical homogeneity. Shoulder periarthritis has a staged clinical course, and the main therapeutic problem may differ across stages. In the pain-dominant stage, pain, nocturnal pain, and worsening movement limitation are the major clinical concerns. This stage is therefore suitable for evaluating early analgesia and functional preservation. The additional use of TCM meridian differentiation may further reduce heterogeneity in acupoint selection and clinical presentation. It also reflects the diagnostic and therapeutic logic commonly used in acupuncture practice.

### Acupoint selection rationale

3.1

The acupoint prescription in this trial follows the principles of local acupoint selection, meridian-based acupoint selection, and distal acupoint selection. Jianyu (LI15), Binao (LI14), and Jianliao (SJ14) are located around the shoulder joint and proximal upper arm. These acupoints are close to the main sites of pain and movement limitation and are consistent with the clinical principle of local acupoint selection for shoulder periarthritis. Jianyu (LI15) and Jianliao (SJ14) have also been frequently used in previous acupuncture studies on frozen shoulder (13).

Qinglengyuan (SJ11) and Waiguan (SJ5) are associated with the Hand Shaoyang meridian. Their use is consistent with the inclusion of participants with the Hand Shaoyang meridian pattern. Tiaokou (ST38) is a commonly used distal acupoint for shoulder pain and restricted shoulder movement. It reflects the principle of distal acupoint selection and helps form a local-distal acupoint combination with the shoulder acupoints (33). Therefore, this trial uses a fixed acupoint prescription that is consistent with TCM meridian differentiation and common clinical acupoint selection. This approach may reduce heterogeneity caused by individualized acupoint selection and improve the standardization and reproducibility of the intervention.

### Analgesic rationale for comparing 2 Hz and 100 Hz EA

3.2

Electroacupuncture frequency is one of the most easily quantified and standardized parameters in EA treatment. It is also an important variable that may influence analgesic effects. Previous studies have suggested that different EA frequencies may act through different endogenous opioid peptides, opioid receptors, and descending pain-modulatory mechanisms. Low-frequency EA is more closely related to *μ*- and *δ*-opioid receptor-mediated mechanisms, whereas high-frequency EA may involve *κ*-opioid receptor-related pathways (16–20).

In clinical research, direct comparisons between single-frequency 2 Hz and 100 Hz EA remain limited. Existing evidence mainly comes from studies on postoperative pain (34), chronic low back pain or lumbar osteoarthritis (35, 36), and chemotherapy-induced peripheral neuropathy (37). Preclinical studies using tail-flick, ankle sprain, post-incision pain, diabetic neuropathic pain, inflammatory pain, spared nerve injury, and nerve cuffing models also suggest that 2 Hz and 100 Hz EA may show model-dependent analgesic profiles (17, 20, 38–44). Relevant evidence from clinical trials and animal studies is summarized in Table 3.

**Table 3 tab3:** Clinical and preclinical evidence related to the analgesic effects of 2 Hz and 100 Hz electroacupuncture.

Reference	Disease type/pain model	Frequency setting	Main findings
Lin et al.^a^ (34)	Postoperative pain after lower abdominal surgery	2 Hz, 100 Hz, sham EA, and control	Both 2 Hz and 100 Hz EA reduced postoperative analgesic requirements. The 100 Hz regimen appeared to show greater effects on some analgesic outcomes.
Trinh et al.^a^ (35)	Chronic low back pain related to lumbar osteoarthritis	100 Hz vs. 2 Hz	The 100 Hz group showed a greater reduction in pain score and a higher pain-relief proportion than the 2 Hz group.
Torres et al.^a^ (36)	Chronic nonspecific low back pain in older adults	100 Hz, 2 Hz, alternating 2/100 Hz, manual acupuncture, and placebo control	No EA frequency showed clear superiority. Pain intensity decreased in all groups, and EA was not superior to manual acupuncture or placebo.
Lu et al.^a^ (37)	Paclitaxel-induced peripheral neuropathy	2 Hz, 100 Hz, alternating 2/100 Hz, and medication control	Different EA frequency regimens improved some symptoms. The 2 Hz and alternating 2/100 Hz regimens showed potential advantages in some sensory or pain-related outcomes.
Chen and Han^b^ (17)	Acute nociceptive pain in rats (tail-flick test)	2 Hz, 100 Hz, and 2–15 Hz	Analgesia induced by 2 Hz and 100 Hz EA may be mediated by different opioid receptor mechanisms.
Han et al.^b^ (38)	Acute nociceptive pain in rats (tail-flick test)	2 Hz vs. 100 Hz	Endomorphin-1 mediated 2 Hz, but not 100 Hz, EA-induced analgesia.
Hahm^b^ (39)	Rat ankle sprain model	2 Hz vs. 100 Hz	Both 2 Hz and 100 Hz stimulation produced analgesic effects. The 2 Hz regimen showed a more marked effect on edema.
Fais et al.^b^ (40)	Rat post-incision pain model	2 Hz vs. 100 Hz	Both 2 Hz and 100 Hz EA produced antihyperalgesic effects. The 2 Hz effect lasted longer, whereas amitriptyline potentiated the 100 Hz effect more strongly.
Silva et al.^b^ (41)	Rat post-incision pain model	2 Hz and 100 Hz	Preoperative 100 Hz EA showed a preemptive effect against post-incision pain, whereas postoperative 2 Hz EA appeared more effective.
He et al.^b^ (42)	Type 2 diabetic neuropathic pain in rats	2 Hz vs. 100 Hz	Both 2 Hz and 100 Hz EA alleviated diabetic neuropathic pain, but 2 Hz produced stronger analgesic effects.
Fang et al.^b^ (43)	CFA-induced inflammatory pain in rats	2 Hz, 100 Hz, and 2/100 Hz	Different EA frequencies produced analgesic effects. The 100 Hz effect was stronger than the 2 Hz effect and was associated with TRPV1/P2X3 regulation.
Du et al.^b^ (44)	SNI-induced neuropathic pain in rats	2 Hz vs. 100 Hz	Both 2 Hz and 100 Hz EA improved neuropathic pain. The 2 Hz regimen showed stronger modulation of TRPV1/P2X3 expression.

Superscript a indicates a clinical trial, and superscript b indicates an animal study. CFA, complete Freund’s adjuvant; EA, electroacupuncture; P2X3, purinergic receptor P2X3; SNI, spared nerve injury; TRPV1, transient receptor potential vanilloid 1.

These findings indicate that both 2 Hz and 100 Hz EA have a basis in analgesic research. However, the relative advantages of different frequencies may vary according to pain type, disease stage, stimulation timing, and outcome measures. In pain-dominant shoulder periarthritis, direct clinical trial evidence comparing 2 Hz and 100 Hz EA remains lacking. This head-to-head trial will address this specific evidence gap and may help clarify frequency selection for EA in this disease stage.

### Intervention standardization and outcome selection

3.3

This trial will keep all intervention factors as consistent as possible between the two groups, except for EA frequency. These factors include acupoints, needle specifications, insertion methods, de qi requirements, connected acupoints, waveform, needle retention time, treatment frequency, TDP irradiation, and treatment setting. This design will help isolate EA frequency as the key variable and reduce confounding from other treatment factors.

Both groups will receive the same TDP irradiation. Therefore, this trial will evaluate the relative efficacy of 2 Hz and 100 Hz EA under the same co-intervention setting. It will not evaluate the independent effect of TDP or the absolute efficacy of EA compared with no treatment, usual care, or sham acupuncture.

The VAS is selected as the primary outcome because pain is the most direct and core clinical manifestation of pain-dominant shoulder periarthritis, and it provides a simple validated measure of pain intensity (27). SPADI, CMS, and ROM will be used as secondary outcomes. These measures evaluate patient-reported pain and disability, overall shoulder function, and AROM and PROM, respectively (29–32). This outcome set can capture subjective pain experience, functional limitation, and recovery of shoulder mobility, thereby providing a more comprehensive evaluation than a single pain outcome.

This trial will use several follow-up time points. T1 corresponds to the end of treatment and will mainly assess early analgesic effects after the treatment course. T2 and T3 will be used to observe changes in pain, function, and ROM during short- and medium-term follow-up. Shoulder periarthritis has a staged clinical course, and pain relief, functional improvement, and ROM recovery may not occur at the same pace. Repeated assessments at multiple time points may help characterize the time course of treatment effects for different EA frequencies and provide evidence for evaluating the durability of treatment effects.

